## Abstract

**Background:**

Children in low and middle-income countries (LMICs) are at risk for problems in their cognitive, social and behavioural development. Factors such as a lack of cognitive stimulation, harsh parenting practices, and severe and persistent aggression in early childhood are central to the genesis of these problems. Interventions that target the intersection between early childhood development, parenting, and early violence prevention are required in order to meaningfully address these problems.

**Methods:**

We are conducting a randomised controlled trial to evaluate a parenting intervention for caregivers of children aged between 23 and 27 months, designed to promote child cognitive and socioemotional development in Khayelitsha, a low-income peri-urban township in South Africa. Families are randomly allocated to a book-sharing intervention group or to a wait-list control group. In the intervention, we train caregivers in supportive book-sharing with young children. Training is carried out in small groups over a period of 8 weeks. Data are collected at baseline, post intervention and at 6 months post intervention. In addition to targeting child cognitive development, the intervention aims to improve child socioemotional functioning.

**Discussion:**

The Benefits of Early Book Sharing (BEBS) trial aims to evaluate the impact of an early parenting intervention on several key risk factors for the development of violence, including aspects of parenting and child cognition, prosocial behaviour, aggression, and socioemotional functioning. The study is being carried out in a LMIC where violence constitutes a major social and health burden. Since the intervention is brief and, with modest levels of training, readily deliverable in LMIC contexts, a demonstration that it is of benefit to both child cognitive and socioemotional development would be of significance.

**Trial registration:**

The BEBS trial is registered on the International Standard Randomised Controlled Trial Number database, registration number ISRCTN71109104. Registered on 9 February 2016. This is version 1 of the protocol for the BEBS trial.

**Electronic supplementary material:**

The online version of this article (doi:10.1186/s13063-017-1790-1) contains supplementary material, which is available to authorized users.

## Background

### Child development problems in low and middle-income countries (LMICs)

Children in low and middle-income countries (LMICs) are at risk for problems in their cognitive, social, and behavioural development [1]. These risks carry not only a considerable social burden, but also have a major adverse financial impact on affected societies [2]. These children’s problems commonly occur in the context of widespread poverty. Indeed, conservative estimates suggest that in excess of 200 million children, primarily in sub-Saharan Africa and Asia, are failing to reach their developmental potential as a result of such poverty [1]. What makes optimal development so difficult for young children to achieve in these contexts is a combination of adverse factors that impair cognitive, social and emotional development, as well as physical growth and health [3]. These predominantly occur within a context of severe community stress, often characterised by high levels of aggression and violent crime, and lack of opportunities for escape from disadvantage. In this context, caregivers who themselves have been educationally and socially disadvantaged are likely to replicate childrearing and relationship practices that contribute to cognitive and socioemotional deficits and behaviour problems [3].

### Cognitive development

A large body of research from high-income countries (HICs) has shown that early cognitive development is a critical determinant of subsequent school progress and literacy [4–6]. Evidence suggests that a similar relationship obtains in LMIC settings [7–9]. Hence, the early developmental deficits so prevalent in LMIC contexts are likely to play a critical role in how cycles of poverty and deprivation become entrenched in societies through their adverse impact on educational progress, and thereby on future employment opportunities and earning potential [2, 10]. South Africa is particularly relevant in this regard, as recent evidence on educational outcomes has shown that children are performing exceptionally poorly, even when compared to other LMICs [11]. Notably, there appears to have been a steady worsening over recent years of school grade scores on measures of reading and literacy [12]. Importantly, both cross-sectional and longitudinal research shows that particular parenting practices are associated with child cognitive performance: where parental interactions are responsively contingent to the child, and support the child’s active engagement in their environment, children perform better on measures of cognitive functioning [13, 14].

### Violence and aggression

Aside from cognitive and socioemotional delays, a major problem that disproportionately affects those in LMICs is a high rate of community violence. Indeed, violence is one of the leading causes of premature morbidity and mortality in LMICs, with homicide rates often up to 30 times higher than in HICs [15]. In South Africa, violence has been reported as the second highest contributor to deaths and disability-adjusted life years (DALYs) after HIV/AIDS [16]. Longitudinal evidence shows that the perpetration of violence is predicted by the development of severe and persistent aggression in early childhood [17–19]. Such a trajectory is likely to arise when young children do not acquire adaptive ways of dealing with challenges and frustrations.

Studies in HICs show that aggression in childhood and adolescence is predicted by a range of early child, family, and wider social factors [7, 13, 14]. Key predictors include child concentration problems and hyperactivity, as well as insecure attachment [17]. Importantly, meta-analyses have also revealed the importance of particular parenting problems, namely, the occurrence of harsh and coercive parenting, including corporal punishment, and the lack of parental positive reinforcement and responsiveness, and general insensitivity [20, 21]. Although little is known about parenting and family risk factors for violence in LMICs, the available evidence suggests that the same predictive relationships obtain as in HICs [22, 23].

In addition to evidence concerning the early child and parenting *risks* for later aggression, research has shown a number of early positive child and parenting characteristics to be associated with *reduced* levels of aggression. One key child characteristic is social understanding. This includes the ability to understand one’s own feelings, emotions, desires and intentions, as well as those of other people [24]. A key development in early social understanding is ‘theory of mind’ – the ability to accurately attribute mental states (desires, motives, emotions) to other people and understand that these can be different from one’s own [25]. The development of social understanding is important because it underpins cooperation and prosocial behaviour [24] which, in turn, predict lower rates of aggression and externalising behaviour problems [26, 27].

As with child cognition and aggression, specific aspects of early parenting are important in the development of child social understanding. In particular, research has highlighted the contribution of specific kinds of parental discourse with the child because these are internalised and shape child socioemotional development [28, 29]. When parental speech includes frequent reference to mental states, desires and emotions (e.g. ‘think’, ‘feel’, ‘want’), this helps to promote children’s social understanding, including theory of mind capacity [30, 31].

### Book-sharing

The sharing of picture books with young children is well-established as being of substantial benefit to their language development and preliteracy skills [32–34]. An early meta-analysis of the frequency of parent-child book-sharing on language development, emergent literacy, and reading achievement revealed an overall effect size of *d* = 0.59 on collective language and literacy outcomes [35]. Intervention studies in HICs in which carers have been trained in supportive book-sharing skills have found that this leads to substantial improvements in child cognitive outcomes [36–38]. A more recent meta-analysis assessed the value of dialogic reading interventions and included observational studies, quasi-experiments, and randomised controlled trials [32]. This review showed an overall effect on child vocabulary outcomes of *d* = 0.42; CI 0.30, 0.53. Finally, a recent meta-analysis on the effectiveness of shared picture-book reading interventions on child language outcomes revealed a substantial effect on expressive vocabulary (*d* = 0.57; CI 0.33, 0.81) and a positive, although more modest, effect on receptive language (*d* = 0.26; CI 0.12, 0.41) [39].

Picture books that are rich in mental themes can also be effective tools for prompting mental state discussion between parents and young children [40–42]. Indeed, recent observational research has also shown associations between book-sharing and child social understanding [43, 44]. Thus, there is preliminary evidence that not only is book-sharing a good context in which carers can promote the development of child cognitive skills, but it is also a particularly appropriate context for parents to talk about mental states and thereby promote child social understanding [44].

To date, there is little evidence concerning the benefits of training parents in book-sharing in LIMCs. However, in a randomised trial of a book-sharing intervention we recently conducted in South Africa, with carers of 14–16-month-old infants, we demonstrated substantial gains in infant language and attention [45], and found preliminary evidence of improvements in social understanding and empathy [46]. Notably, mediation analyses showed that it was by virtue of improvements in parental sensitivity and reciprocity that the cognitive gains were brought about [46].

### Current trial

Our previous book-sharing trial [45, 46] focussed on promoting child language and attention. In the current trial the intervention includes a more specific focus on promoting parenting skills relevant to child social understanding and aggressive behaviour. Specifically, the training is extended to include book content with themes concerning book characters’ emotions, intentions, perspectives, and prosocial behaviour, in order to promote parental mental state and emotion talk around these topics. Although we do not directly address the topic of negative parenting in the intervention, we hope to reduce such practices generally as a secondary consequence of promoting positive parenting characteristics in the context of book-sharing.

## Methods

### Study design

We are conducting a randomised controlled trial (RCT) to evaluate a book-sharing intervention for caregivers of children aged between 23 and 27 months designed to promote child cognitive and socioemotional development. Participants are randomised at the individual level to an intervention or a wait-list control group. Data are collected at baseline, post intervention and at follow-up. Figure 1 presents a Standard Protocol Items: Recommendations for Interventional Trials (SPIRIT) representation of the study design. The SPIRIT guidelines for study protocols were followed and a populated SPIRIT checklist is included (see Additional file 1).

**Fig. 1 Fig1:**
[figure not shown]
Schedule of enrolment, interventions and assessments. Standard Protocol Items: Recommendations for Interventional Trials (SPIRIT) figure displaying schedule of enrolment, interventions and assessments

Hypotheses:

Primary hypotheses:Compared to control-group children whose carers receive no intervention, those whose carers receive the programme will evidence significantly better outcomes on measures of language and sustained attentionCompared to control-group children, intervention-group children will evidence significantly more prosocial behaviour and less aggression

Secondary hypotheses:3.Compared to control-group children, intervention-group children will evidence significantly better social understanding4.Compared to control-group caregivers, caregivers who receive the programme will evidence significantly more sensitivity, reciprocity, and mental state talk with their children, both in book-sharing and non-book-sharing contexts5.Compared to control-group caregivers, caregivers who receive the programme will evidence significantly less negative and more supportive parenting in challenging contexts6.Improvements in child language and attention will be mediated by improvements in maternal sensitivity and reciprocity in the book-sharing context, and7.Improvements in child social understanding, prosocial behaviour and aggression will be mediated by increases in maternal sensitivity and mental state talk in both book-sharing and non-book-sharing contexts, and by a reduction in negative parenting and an increase in supportive parenting in challenging contexts

### Study setting

The study is being conducted in Khayelitsha, a large peri-urban township on the outskirts of Cape Town, South Africa. It is characterised by high levels of poverty, unemployment and violence [47]. All assessments take place at the Prevention Research for Community, Family and Child offices at the Masiphulisane Community Development Centre. Intervention group sessions are held in a church hall connected to the Masiphulisane Centre.

### Eligibility criteria

Families who are eligible for inclusion in the study are those with children aged 23–27 months at the time of baseline assessment. They also require an adult primary caregiver who is at least 18 years old, lives in the household with the child for at least four nights per week, and who consents to participate in the study. A chronic illness or disability in the child or the adult that would prevent them from fully participating in the intervention is an exclusion criterion.

### Sample size

A minimum of 140 caregiver-child dyads (70 in each arm) will form the study sample. The sample has considerable power to detect the primary cognitive outcomes and adequate power to detect the primary behavioural ones. The sample size has been calculated using available appropriate effect size estimates on the primary outcomes.

#### Power calculation

All power calculations have been run for 80% power and alpha = 0.05. The power calculation for primary outcomes of language and attention was based on previous research that aimed to improve child language and focal attention through a book-sharing intervention in South Africa [45]. The effect size on sustained attention was *d* = 1.1, and the effect size on receptive language was *d* = 0.73. Based on these figures, two groups of 13 are sufficient to detect the established difference on the attention variable, and two groups of 44 are sufficient to detect the established difference on the language variable. For the behavioural outcomes of aggression and prosocial behaviour, the power estimates were based on normative data from a study in Khayelitsha on a sample of 302 children. For prosocial behaviour the mean was 7.39 (SD = 2.08) and for aggression it was 12.84 (SD = 7.18). As such, for both the prosocial and the aggression variables, two groups of 64 are sufficient to detect the difference (two-tailed), based on an effect size of 0.50. Two groups of 70 are, therefore, being recruited, which allows for 10% sample attrition.

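### The language sample size of 44 per group does not follow from d = 0.73 at 80% power and alpha 0.05, which needs 31 per group; a small misstatement of tolerated attrition should be corrected with it

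*Protocol article*

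**What the plan says.** The Power calculation section opens with common settings: "All power calculations have been run for 80% power and alpha = 0.05". For the cognitive primary outcomes it takes effects from the group's previous book-sharing trial in South Africa. Attention is given an effect of d = 1.1, from which 13 per group are derived. For the other cognitive outcome, the section reports that "the effect size on receptive language was *d* = 0.73". Its conclusion from that value is that "two groups of 44 are sufficient to detect the established difference on the language variable".

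For prosocial behaviour and aggression it states that "two groups of 64 are sufficient to detect the difference (two-tailed), based on an effect size of 0.50". The paragraph ends by turning these requirements into a recruitment target: "Two groups of 70 are, therefore, being recruited, which allows for 10% sample attrition".

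The Sample size section draws the conclusion from these figures: "The sample has considerable power to detect the primary cognitive outcomes and adequate power to detect the primary behavioural ones".

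**The concern.** All the inputs for the language calculation are printed next to its result, so a reader can repeat it. A standardised effect of 0.73 is large enough that about 30 per group suffice for 80% power. The printed 44 is 13 more than 31, an excess of 13/31 = 42%. Rounding, or the choice between a t test and a normal approximation, moves such a figure by one or two, not by 13.

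Language is a primary outcome, and this is the only sample-size figure given for it. If the group size is the wrong number, the remedy is a one-word correction. If the effect size is the wrong number, the article overstates the earlier trial's effect on a primary outcome, and 0.73 may be carried into later planning or into the interpretation of this trial's result.

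The attrition sentence has a smaller fault of the same kind: the stated loss takes each arm just below the number that the section itself says is needed.

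**Working it through.** **Inputs.** From Power calculation: power 0.80; alpha 0.05; d = 1.1 (attention), 0.73 (language) and 0.50 (behavioural); stated sizes of 13, 44 and 64 per group; 70 per arm recruited; 10% attrition. From Randomisation: 1:1 allocation. Two-sided testing is stated only for the behavioural outcomes, and I assume it for the others.

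**Formula.** The normal approximation for two equal groups is n = 2(1.96 + 0.8416)² / d² = 15.70 / d² per group. The t-test figure solves the same problem with the noncentral t distribution and is slightly larger.

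**Reproducing the plan's figures.**

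| Outcome | d | Stated | Normal approximation | t test |
|---|---|---|---|---|
| Attention | 1.1 | 13 | 15.70/1.21 = 12.97, so 13 | 14.002, so 15 |
| Language | 0.73 | 44 | 15.70/0.5329 = 29.5, so 30 | 30.45, so 31 |
| Behavioural | 0.50 | 64 | 15.70/0.25 = 62.8, so 63 | 63.77, so 64 |

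The first and third rows agree with the article within rounding. The language row does not.

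**What 44 per group would mean.**
- Two-sided t-test power at d = 0.73 with 44 per group is 92.3%.
- With 44 per group, alpha 0.05 and 80% power, the detectable effect is d = 0.604.

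**Could another setting give 44 at d = 0.73?**
- One-sided, 80% power: 24 per group, further away.
- Two-sided, 90% power: 41. Two-sided, 95% power: 50.
- One-sided, 95% power: 42.
- Inflating for a Mann-Whitney test (relative efficiency 0.955 or 0.864): 32 or 36.
- Two-sided alpha of 0.05/4 = 0.0125, 80% power: 44. This contradicts the stated alpha, and on the same basis attention would need 21, not 13.

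Nothing within the stated settings returns 44.

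**Effect on the enrolled sample.** The largest requirement, 64 per group at d = 0.50, sets the target. With 63 per arm (70 less 10%), power at d = 0.73 is 98.2%.

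**Attrition.**
- 70 × 0.90 = 63, one below 64.
- The largest loss that keeps 64 is 6 of 70, and 6/70 = 8.6%.
- 64/0.90 = 71.1, so exact inflation for 10% loss gives 72 per arm.
- Power at d = 0.50 with 63 per arm is 79.5% by t test and 80.1% by the normal approximation. With 64 per arm the t test gives 80.1%.

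**The case against.** The strongest reply is that nothing turns on the 44. The article claims only sufficiency, and 44 per group is more than sufficient for d = 0.73. The figure does not set the target, power for language is about 98% even after 10% loss, and recruitment has ended. If the effect size is the misprint and the source value is near 0.60, then 44 is right. All of this stands, and it limits the point to a correction of text. It does not make the printed pair consistent: the section presents its sizes as those required at 80% power, and 13 and 64 are such minimum sizes while 44 is not.

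On attrition, the reply is that 64 × 1.1 = 70.4, so 70 reflects the common habit of adding 10%, and the gap is one dyad per arm. Also, 79.5% is the power of an unadjusted t test, whereas the Data analysis section plans analysis of covariance with baseline score, age and sex. The article gives no baseline-outcome correlation. If it were 0.2, 0.3 or 0.5 (assumed values), power at 63 per arm would be about 81%, 83% or 90%. This also stands, and it is why the attrition point is only a companion correction.

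A reader might infer that the power section fails as a whole, or that the trial is underpowered for its behavioural outcomes. The document supports neither. The 13, the 64 and the 70 reproduce within rounding, and half a percentage point below 80% on an unadjusted test is not a material shortfall. A lower figure that allowed for clustering in the intervention groups would need an intraclass correlation, which the article does not give. Nor is the 0.50 disguised: the text openly gives it as the effect size used.

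**Conclusion.** The language calculation is wrong as printed. At the stated power and alpha, d = 0.73 needs 31 per group (two-sided t test; 30 by the normal approximation), not 44. Conversely, 44 per group matches d of about 0.60 and gives 92% power at 0.73. The effect size, the alpha or the group size is misreported, and the source trial would have to be consulted to say which. The conclusion assumes two-sided testing; one-sided testing widens the gap.

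The error is conservative. It changes neither the 70 per arm nor the claim of considerable power for the cognitive outcomes.

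The attrition sentence overstates its allowance slightly: 8.6% rather than 10%, or 79.5% unadjusted power after 10% loss. Both are minor corrections of fact, and neither is evidence of an inadequate sample.

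**What to change.** Check the receptive-language effect in the source trial, then restate one of the two figures:
- if d = 0.73 is correct, give 31 per group; or
- if 44 per group was calculated from a different effect, give that effect, which should be about d = 0.60.

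If a different alpha was used for language, say so and bring the common-settings sentence and the attention figure into line with it.

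In the same edit, replace the attrition statement with one that matches the arithmetic: either 70 per arm retains the required 64 with up to about 8.6% loss, or unadjusted t-test power at d = 0.50 after 10% loss is 79.5%.

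The cost is one look-up and two sentences. Enrolment, design and analysis are unaffected. The stated attrition allowance becomes slightly less favourable.

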### Recruitment

Recruitment began in February 2016 and ended in August 2016. Participants were recruited from four neighbourhoods within the greater Khayelitsha region. Three of these neighbourhoods fall within the area of Endlovini which consists almost entirely of informal housing structures. One area is located in Makhaza which is characterised by a mix of formal brick housing and informal structures. Recruitment took place in two consecutive waves. Recruiters systematically visited each house in the demarcated area and enquired about potentially eligible participants. Participants who met inclusion criteria and were interested in being part of the study were invited to the research centre.

